## Abstract

**Background:**

Diabetic foot ulcer (DFU) is one of the most common and serious complications of diabetes mellitus (DM). The high disability and fatality rates of DFU raise the importance of early medical treatment. However, delays in seeking medical treatment among DFU patients are common, emphasizing the need for targeted health education. This study aims to evaluate the effectiveness of a Multi-Theory Model (MTM)-based foot care education program on improving healthcare decision-making and foot care behaviors in diabetic patients with risk of foot ulceration.

**Method:**

A multicenter randomized controlled trial will be employed. Diabetic patients at risk of foot ulceration will be recruited from two different tertiary hospitals in different cities. Eligible participants will be randomly allocated to receive either routine education and a foot-care handbook (control group) or comprehensive foot-care education based on MTM (intervention group). The intervention period will last for 4 weeks, followed by a 3-month post-intervention follow-up. Questionnaire data and clinical data will be collected at baseline, immediately after the 4-week intervention, and at the 3-month follow-up. The primary outcome will be pre-hospital delay intentions. Foot care knowledge, foot care self-efficacy, and foot care behaviors will be investigated using questionnaires. Clinical data, including blood glucose, blood pressure, and body mass index (BMI), will also be assessed.

**Discussion:**

Based on the MTM, this study developed a comprehensive foot-care education program for diabetic patients at risk of foot ulceration. By integrating systematic, theory-driven educational components, the program may equips both hospitals and community health services with a structured approach to deliver targeted foot-care education.

**Trial registration The RCT registry number:** ChiCTR2400082853, 09/04/2024.

## Introduction

Diabetes mellitus (DM) is one of the most prevalent chronic diseases worldwide, posing a significant challenge to public health and has been a serious health problem. Epidemiological data from the International Diabetes Federation (IDF) indicates a global prevalence of 10.5% (536.6 million) among adults aged 20–79 in 2021, with a projected increase to 12.2% (783.2 million) by 2045 [1]. The clinical management of DM is complicated by the development of systemic sequelae, among which the diabetic foot ulcer (DFU) is one of the most severe. It is defined as an ulceration associated with neuropathy and/or peripheral arterial disease in the lower limb of a diabetic patient [2]. Every patient with DM has a 19–34% risk of developing a DFU at some point during their lifetime [3]. The global annual incidence is estimated to be between 9.1 and 26.1 million cases, highlighting its substantial burden on healthcare systems [1].

DFU poses a significant societal burden due to its substantial economic impact and severe clinical outcomes. Inadequate management leads to high costs for patients, families, and healthcare systems [4]. Clinically, approximately 20% of DFU patients undergo lower extremity amputation [5]. Moreover, DFU is associated with a significantly increased risk of mortality, with patients facing a 2.45 times higher risk of death compared to diabetic patients without foot ulcers [6].

The high mortality and disability rates associated with DFUs underscore the importance of prevention and seeking medical care promptly. Clinical guidelines suggest that patients should access specialized multidisciplinary care immediately after discovering an ulcer to decrease the likelihood of amputations and reduce the risk of mortality [7–10]. The National Institute for Health and Care Excellence (NICE) specifically advises that patients be referred to a multidisciplinary team within 24 hours of identifying a foot problem [11]. Nonetheless, a considerable number of patients fail to seek care during this critical window. Consequently, more than 50% of patients present with a diabetic foot infection (DFI) at their initial clinical visit, indicating a significant delay in obtaining the necessary medical intervention [12].

Substantial delays exist in the management of DFUs. The median time from symptom onset to specialist assessment ranges from 15 to 126 days, with a further median delay of 1–91 days from assessment to treatment initiation [13]. In China, this problem is severe, with pre-hospital delay rates ranging from 80.8% to 95.6% and a mean delay of 54.81 days before patients seek care [14]. A survey by Jun et al. [15] reported that among the diabetic patients who had foot problems in the past year, only 14.85% of them sought medical attention. Li et al. [16] found that only 33.2% of diabetic patients sought medical treatment within 1 week of DFU onset, while 48.7% saw a doctor within 2 weeks, with a median pre-hospital delay of 14 (range 1–354) days. These findings indicate substantial pre-hospital delays and prolonged visit times among patients with DFUs.

Delay in seeking medical assistance has been identified as an independent risk factor for poor outcomes among diabetic patients with limb complications [17]. It increases the risks of amputation and death [18]. Specifically, each 1 day delay in seeking medical care for DFUs is associated with a 3.5% increase in toe amputation (toe) rates [19]. As a result, it is suggested that a more aggressive and tailored education approach, which guides patients to act quickly in seeking medical care, is needed [20].

Evidence confirms that interventions integrating multiple theoretical approaches are more effective [21–23]. In this study, Multi-Theory Model (MTM) for health behavior change has been introduced. It overcomes the shortcomings of previous models by providing a dedicated framework for health behavior change and allowing for the study of long-term behavioral maintenance [24]. The MTM is structured in two components: behavior change initiation and sustenance. The initiation of behavior change is governed by three constructs: (1) participatory dialogue, where perceived benefits of a new behavior must outweigh its disadvantages; (2) behavioral confidence, or the belief in one’s capability to perform the behavior, derived from both internal and external sources; and (3) changes to the physical environment to provide tangible resources [24,25]. The sustenance of behavior change is similarly supported by three constructs: (1) emotional transformation, the ability to direct emotions toward a goal; (2) practice for change, which entails continuous, deliberate effort and adjustment of strategies; and (3) changes in the social environment, involving the creation of a supportive network, often facilitated by health educators.

This study will develop a foot-care education program based on MTM, and then employ a randomized controlled trial to evaluate its effectiveness among diabetic patients at risk of DFU.

### Aim and hypothesis

We aimed to investigate the effectiveness of an MTM-based foot-care education program in reducing patients’ pre-hospital delay intention and improving their foot-care knowledge, self-efficacy, and behaviors, as well as enhancing foot health and indicators including blood glucose and blood pressure.

It is hypothesised that, compared with those receiving foot-care handbook and routine education, the intervention group, who receive MTM-based foot-care education program, will have significantly strength in:

Reducing pre-hospital delay intention.Improving foot-care knowledge, foot-care self-efficacy, and foot-care behavior.Improving foot health.Improving blood glucose and blood pressure.

## Methods

### Study design

This is a protocol of a randomized study in which a foot-care education program based on MTM will be implemented among diabetic patients at risk of foot ulceration. The study is an assessor-blined two-arm RCT. We used the SPIRIT guidelines to guide reporting of our trial protocol [26]. It has been registered in Chinese Clinical Trial Registry (No. ChiCTR2400082853).

### Location and setting

The study will be conducted at 2 different tertiary hospitals in Yangzhou and Nanjing, Jiangsu province.

### Participants and eligibility criteria

The study will recruit diabetic patients at risk of foot ulceration from a hospital setting. Participants must meet the World Health Organization diagnostic criteria for DM [27] and the risk criteria outlined in the Guidelines for the Diagnosis and Treatment of Diabetic Foot [28,29]. The inclusion criteria will be as follows: a) diagnosis of DM without an active foot ulcer, presenting with diabetic peripheral neuropathy (DPN), with or without foot deformity, peripheral artery disease, or a history of foot ulceration or amputation; b) age ≥ 18 years; c) possession and functional use of a smartphone with WeChat by both patient and caregiver; d) absence of communication-impairing conditions (e.g., hearing loss, aphasia, unconsciousness, psychiatric disorders); and e) provision of written informed consent. Exclusion criteria will include: a) severe concomitant conditions (renal impairment ≥ stage IV, cardiac function ≥ class III, or severe cerebrovascular disease); b) pregnancy or gestational diabetes; c) peripheral neuropathy attributable to non-diabetic causes (e.g., severe hepatic/renal disease, nutritional deficiencies, connective tissue disorders); and d) concurrent participation in another clinical trial.

### Sample size calculation and allocation

The sample size was calculated using G*Power 3.1 software for a two independent samples t-test. The primary outcome was pre-hospital delay intention (PHDI). A large effect size (Cohen’s d = 0.80) was adopted, which was justified by a previous study in patients with high-risk diabetic foot that reported a large effect size on pre-hospital delay intention [30]. The type I error rate (α) was set at 0.05 (two-tailed), and the statistical power (1 − β) was set at 0.85 [31]. The calculation yielded a required sample size of 30 participants per group. Accounting for an anticipated 15% attrition rate during follow-up, the final target sample size was set at 35 patients per group (total N = 70).

All the participants will be randomly divided into control group (n = 35) and intervention group (n = 35) upon admission. Randomization will be performed automatically by Microsoft Excel at enrollment. The “RAND ()” function in Microsoft Excel will be used to generate a series of random numbers by an independent researcher and kept in a sealed, opaque envelope. These numbers will be served as the basis for patient allocation into either the control group or intervention group.

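### The protocol fixes 35 patients per arm but gives no rule from Excel random number to arm, describes two allocation mechanisms that do not fit together, and leaves hospital out of both allocation and the stated model

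*Protocol article*

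**What the plan says.** All of the allocation text is in Sample size calculation and allocation. It sets the arms at 35 control and 35 intervention patients. It then gives two accounts of how patients reach them:

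- "Randomization will be performed automatically by Microsoft Excel at enrollment".
- The RAND() function is used to "generate a series of random numbers by an independent researcher and kept in a sealed, opaque envelope". These numbers are then said to underlie the assignment of each patient.

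No ranking, cut-off, block size, stratum or separate list per hospital is mentioned.

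Under Location and setting: "The study will be conducted at 2 different tertiary hospitals in Yangzhou and Nanjing, Jiangsu province". The abstract also calls the trial multicentre.

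Statistical analyses specifies a repeated-measures analysis of variance on the raw values at three time points. Group is the between-subjects factor and time the within-subjects factor. Hospital appears neither as a factor nor as a covariate.

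**The concern.** Three things do not close.

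1. **The arm sizes have no stated mechanism.** Exact 35:35 needs a restriction, such as ranking the numbers and cutting the list in half, or blocking. The text names none.
2. **The two mechanisms differ.** Allocation computed automatically at enrolment needs no envelope. A list prepared in advance by someone independent and held in an envelope is not automatic at enrolment. They also carry different concealment risks, so a reader cannot tell what will be done.
3. **Hospital is handled nowhere.** The control condition is each setting's routine education, which may differ between two hospitals in different cities, and the primary outcome is a questionnaire score. With 70 patients, the arms may by chance draw unequally on the two hospitals, and the stated model does not adjust for that.

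At stake are the credibility of the allocation procedure and some precision, plus a chance hospital imbalance that the stated analysis would leave uncorrected.

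**Working it through.** **Inputs from the protocol article.** Two-sided α = 0.05; "the statistical power (1 − β) was set at 0.85"; "A large effect size (Cohen’s d = 0.80) was adopted"; two-sample t-test; 15% attrition; N = 70 as 35 + 35; two hospitals. The split of the 70 between hospitals is not given, so it is assumed and varied below.

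**Reproducing the plan's own figure.** The two-sample t-test (noncentral t) with d = 0.80 needs 29.05 per group, rounded up to 30. This agrees with "The calculation yielded a required sample size of 30 participants per group". For attrition, 30 × 1.15 = 34.5, rounded up to 35, is the stated target; 30 / 0.85 = 35.3 would round up to 36. The difference is immaterial here. Power is 91.0% at 35:35, and 85.8% after 15% attrition.

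**Reading A: the list is ranked and cut so that 35 go to each arm.** The overall split is then exact if all 70 places are used. For a hospital contributing H patients, the number X in one arm is hypergeometric:

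P(X = k) = C(35, k) × C(35, H − k) / C(70, H)

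- H = 35 (assumed 35/35 recruitment): P(X ≤ 14 or X ≥ 21), that is 21:14 or worse, = 15.1%. The 95% range is 13 to 22 of 35.
- H = 20 (assumed 50/20 recruitment, smaller hospital): P(X ≤ 8 or X ≥ 12), that is 60:40 or worse, = 42.8%. The 95% range is 6 to 14 of 20.

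**Reading B: one unrestricted draw per patient.** X is Binomial(70, 0.5).

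- P(exactly 35:35) = 9.5%.
- P(smaller arm ≤ 30) = 28.2%.
- P(smaller arm ≤ 26) = 4.1%.
- 60:40 or worse within a hospital: 31.1% for 35 patients, 50.3% for 20.

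**What unequal arms cost (d = 0.80, t-test).**

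| Split | Power, all 70 | Power after 15% attrition |
|---|---|---|
| 35:35 | 91.0% | 85.8% |
| 30:40 | 90.4% | 85.1% |
| 26:44 | 89.0% | 83.4% |

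Even at 26:44 the loss is 2.0 points, or 2.4 after attrition.

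**What hospital imbalance does to the estimate.** Shift in the unadjusted group contrast = (hospital's share of arm 1 − its share of arm 2) × difference between hospitals. Assume the hospitals differ by 0.5 SD and each arm has 35 patients.

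- 21:14 in one hospital: (21/35 − 14/35) × 0.5 = 0.20 × 0.5 = 0.10 SD, one eighth of the planned 0.80 SD.
- 22:13, the edge of the 95% range: (9/35) × 0.5 = 0.13 SD.
- 12:8 in a hospital of 20: (4/35) × 0.5 = 0.06 SD. At 14:6, (8/35) × 0.5 = 0.11 SD.

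So the 43% figure for a small hospital goes with a smaller shift, because that hospital makes up little of either arm.

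These shifts apply to a between-group comparison of levels. In a group-by-time test a stable difference in level between hospitals drops out; only a difference between hospitals in change over time would carry through.

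**The case against.** The article is condensed. Block sizes, strata and centre terms may stand in a full protocol or analysis plan that is not shown, and the article never calls its randomisation simple or unrestricted. This stands in part: that blocking is not described does not prove that none is planned. But the article does set out its allocation method and its model factors, and the mismatch between the two mechanisms is in the text itself.

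Four stronger readings are tempting, and the document does not support them.

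- **That 35:35 will rarely be achieved.** The 9.5% and 28.2% figures hold only for unrestricted draws. The promise of exactly 35 per arm fits a ranked list better, and such a list is neither stated nor excluded.
- **That the result will be confounded by hospital.** Randomisation remains unbiased on average. The concern is an unadjusted chance imbalance of modest size, much of which cancels if the group-by-time term is the test.
- **That allocation is open.** An independent researcher and a sealed, opaque envelope are specified. That there is only one envelope rests on a single singular noun.
- **That each hospital has its own staff delivering the programme.** The article does not say so. It gives the lectures to a trained research team, plans nurse training for consistency and supplies one handbook to all patients.

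**Conclusion.** The point holds as a cheap improvement, not as a threat to the trial's validity. The allocation text promises exact arm sizes without a rule that produces them and describes two mechanisms that must be reconciled. Neither the described allocation nor the stated model deals with hospital.

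On the reading most favourable to the protocol, a ranked list, balance within hospitals is still left to chance: about 15% for 21:14 or worse if each hospital recruits 35, and about 43% for 60:40 or worse in the smaller hospital if recruitment is 50/20. Both recruitment splits are assumptions. The effect on the contrast is about 0.10 SD for a 21:14 split, on a further assumption of a 0.5 SD hospital difference, and less for a group-by-time test unless hospitals differ in change over time. Power is barely affected.

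**What to change.** Before recruitment, which the article describes as not yet begun:

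1. Have the independent researcher generate one permuted-block list per hospital, with randomly varied block sizes (for example 4 and 6). Save it as fixed values, since RAND() redraws on recalculation, and hold it in sequentially numbered, sealed, opaque envelopes.
2. Replace the sentence on automatic allocation at enrolment with this procedure, so that only one mechanism is described.
3. Add hospital as a between-subjects factor in the primary model.
4. State the arm sizes as about 35 each. With blocks of at most 6, the arms differ by at most 3 within a hospital, hence by at most 6 overall (38:32 of 70).

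The cost is a few hours of list preparation and one between-subjects degree of freedom. N stays at 70. The downside is slight predictability at block ends, which matters because the lead investigator is unblinded; varying and not disclosing the block sizes limits it.

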### Blinding

The physician assessing outcome measures, as well as the statistician performing all statistical analysis will be blinded. The patients and the lead investigator in charge of the supervised training cannot be blinded for group allocation due to the nature of the intervention.

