### Changes in the physical environment

Regarding “Changes in the physical environment”, we will provide participants with a bag of foot-care supplies, which includes a cotton towel, a pair of pressure-relief insoles, an infrared thermometer, a toenail file and samples of Vaseline. These supplies are all necessary for foot care. The research nurse will provide verbal persuasion as she shows the patient each item of foot care supplies and review the purpose of each.

In addition, we will also develop a mobile application (app) to provide a software support system for the patients. The smartphone app for diabetes management (register number: 2018SR446465) consists of 4 modules: syndrome differentiation, body differentiation and health preservation, thesaurus, and interactive follow-up. Patients in the intervention group will be required to install the software before hospital discharge. In addition, the research nurses will teach the participants to use the app correctly and ensure that they can use it by themselves.

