### Data collection and management

Following randomization, baseline data will be collected via researcher-administered questionnaires, physical examinations, and biochemical tests. To ensure data quality at this stage, research nurses will check completed questionnaires for completeness immediately after collection.

A key strategy to promote participant retention and complete follow-up involves maintaining regular contact. Participants will receive reminder calls or messages prior to each follow-up assessment. Additionally, we will offer flexible scheduling for follow-up visits and express appreciation for their continued participation. For participants who discontinue the assigned intervention, we will seek their permission to continue collecting some outcome data from their medical records to enable an intention-to-treat analysis.

All paper-based forms will be transcribed into a dedicated electronic database. A comprehensive data management plan will be implemented to ensure data integrity and security. This will include double-data entry for key variables to minimize errors, along with automated range checks for data values to identify outliers. The final dataset will be anonymized and stored on a secure, password-protected computer with regular backups, accessible only to authorized research personnel.

To ensure the validity of the trial and the safety of participants, all patients are allowed to continue their regular diabetic management and must seek immediate care for any acute foot problems. However, participants are not permitted to join other structured foot care programs or trials throughout the duration of this study. The use of newly prescribed specialized footwear for ulcer prevention is prohibited unless it is deemed medically necessary, in which case it must be documented. All such concurrent care is recorded to evaluate its potential impact on the outcomes.

The results will be submitted for publication in peer-reviewed international journals and presented at relevant conferences.

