#### Toronto Clinical Scoring System (TCSS).

The TCSS will be employed to assess DPN. This validated instrument combines evaluation of sensory perception, deep tendon reflexes, and neuropathic symptoms, generating a continuous score from 0 to 19 points [45]. A trained research nurse will administer the assessment using a standardized peripheral nerve testing toolkit.

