### Physical examination

Physical examinations will be performed by trained research nurses using standardized procedures. Participants’ weight and height will be measured using a digital weighing scale and a stadiometer, respectively. Blood pressure measurements will record systolic (SBP) and diastolic (DBP) values using a sphygmomanometer. DFU will be also assessed.

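### The assessor-blinded claim rests on a blinded physician who is given no outcome to assess, while TCSS and the physical examination go to research nurses, a role that also delivers part of the intervention and is not stated to be blinded

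*Protocol article*

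**What the plan says.** The Study design section states: "The study is an assessor-blined two-arm RCT". The Blinding section gives the basis: "The physician assessing outcome measures, as well as the statistician performing all statistical analysis will be blinded". It then lists who is not blinded, as follows: "The patients and the lead investigator in charge of the supervised training cannot be blinded for group allocation due to the nature of the intervention". Research nurses appear in neither list.

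The measurement sections name different assessors. For TCSS: "A trained research nurse will administer the assessment using a standardized peripheral nerve testing toolkit". Under Physical examination: "Physical examinations will be performed by trained research nurses using standardized procedures". That section covers weight, height and blood pressure, and adds in the passive voice that foot ulcer is also assessed.

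On questionnaires, the Data collection and management section says: "Following randomization, baseline data will be collected via researcher-administered questionnaires, physical examinations, and biochemical tests". It adds that "research nurses will check completed questionnaires for completeness immediately after collection". Glucose and HbA1c results are taken from clinical records.

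Research nurses also have delivery tasks. Under Changes in the physical environment they present each supply item with verbal persuasion, and "the research nurses will teach the participants to use the app correctly". Under Changes in the social environment the nurse sends foot-care information over WeChat, and the programme training that is meant to secure consistent delivery is for research nurses.

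**The concern.** Blinding of assessors is a headline validity claim, and readers will give credit for it. Here the one person said to be blinded has no stated measurement task. The people who are given measurement tasks share a role title with those who deliver part of the programme. Staff cannot satisfy the Blinding, TCSS and Physical examination sections together without a rule that the text does not contain.

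The outcomes directly affected are those that an examiner scores or reads: TCSS, which includes sensory testing and reflexes and so involves judgement; blood pressure; and foot ulcer, which is the safety outcome at T2. An assessor who knows the arm, and perhaps taught in it, may score in the direction expected.

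A separate and lesser point concerns the primary outcome. PHDI is a seven-item intention scale answered by patients who know their arm. Blinding an examiner cannot protect that answer, yet the unqualified label may suggest that it does. The Discussion acknowledges self-report but names only recall bias. For a stated future intention, social desirability is the more natural threat.

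**Working it through.** **Step 1. Who assesses what, by section of the protocol article**

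| Outcome | Assessor named | Section | Stated to be blinded? |
|---|---|---|---|
| TCSS | Research nurse | TCSS | No |
| Weight, height, blood pressure | Research nurses | Physical examination | No |
| Foot ulcer | None named; same section as above | Physical examination | No |
| Glucose, HbA1c | Laboratory, taken from records | Blood glucose | Not examiner-scored |
| PHDI, knowledge, self-efficacy, behaviour | Researcher-administered at baseline; no administrator named for T1 or T2 | Data collection and management; Outcome measures | No |
| Any outcome assessed by a physician | None found | – | The physician is the blinded assessor |

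The set of outcomes assigned to the blinded assessor is empty. The set assigned to a named examiner belongs wholly to research nurses.

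**Step 2. Do the named assessors share a role with the deliverers?**
Yes, by title. Research nurses present the supplies, teach the app, send WeChat information and are trained to deliver the programme. The text neither separates delivering nurses from assessing nurses nor says that they are the same people.

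**Step 3. Does the conflict reach PHDI?**
Not by the text. The PHDI section names no administrator. Researcher administration is stated for baseline only, and the nurses' stated task is a completeness check. The bedside counselling on the harm of delay is given by a trained senior nurse, a different title. What does reach PHDI is the openly stated fact that patients are unblinded.

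**Step 4. Size**
The documents give no figure from which a bias could be derived. The following only illustrates how sensitive a trial of this size is to a shift of b standard deviations between arms.

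The inputs from the Sample size section are d = 0.80, two-sided α = 0.05, power 0.85 and a stated 30 per group. For a two-sample t-test with n per group, the noncentrality is d·√(n/2) on 2n − 2 degrees of freedom.

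- The plan's own figure: at n = 30, 0.80 × √15 = 3.10, which gives power 0.861. At n = 29 the power is 0.849. So 30 is the smallest n that reaches 0.85, and the plan's figure reproduces.
- With no true effect and an assumed shift b, the same test at n = 30 rejects as follows:

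| Assumed b (SD) | b × √15 | Rejection rate |
|---|---|---|
| 0 | 0 | 5% |
| 0.1 | 0.39 | 6.7% |
| 0.2 | 0.77 | 11.9% |
| 0.3 | 1.16 | 20.8% |
| 0.5 | 1.94 | 47.8% |

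Every b above zero is an assumption. The test is the one used for planning, at an unadjusted 5% level. It is not the planned repeated-measures analysis with Bonferroni adjustment of secondary outcomes. The finding in Steps 1 and 2 does not depend on this table.

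**The case against.** The strongest reply is that a journal article condenses the full protocol, that assignment of assessors by visit is often left to the full document, and that the schedule figure is not shown. That would answer a complaint about missing detail. It does not answer this one, because the article does name assessors and the names conflict. One might suppose that the physician rates what the nurses record. The text does not say so, and blinding at that later step would not protect a sensory or reflex test scored at the bedside.

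Three stronger readings are tempting, and the documents do not support them.

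- A reader might infer that the nurses who coached patients against delay then record the patients' stated intention to delay. No section says this. The counselling nurse has a different title, the mode for PHDI at T1 and T2 is not given, and a shared title does not show shared individuals.
- A reader might infer that research nurses collect all outcomes. They are named for TCSS and the physical examination. Foot ulcer follows only by its place in that section, and glucose and HbA1c come from records.
- A reader might treat the unblinded patients as a hidden flaw. The Blinding section states it openly, and it is unavoidable in an education trial.

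It also stands that the outcomes with a named nurse examiner are secondary, that foot ulcer is a safety outcome, and that weight on a digital scale leaves little room for judgement.

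**Conclusion.** The contradiction holds for the examiner-assessed outcomes. The Study design and Blinding sections claim assessor blinding through a physician, while the TCSS and Physical examination sections assign the work to a role that also delivers part of the intervention and is not stated to be blinded. As written, the blinding claimed is not in place for TCSS and blood pressure or, reading by section, for foot ulcer.

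For the primary outcome the conclusion is narrower. The assessor-blinded label gives PHDI no protection from patients' knowledge of their arm, and the limitations should say so. The documents do not show that programme staff record PHDI after baseline.

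The size of any bias is unknown, and its direction, probably in favour of the intervention, is a judgement and not a result. The randomisation, the sample size and the analysis model are unaffected. The conclusion rests on the article's text alone; a full protocol that separated the roles would reduce the fix to a correction of wording.

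**What to change.** Reconcile the Study design, Blinding, Data collection and management, TCSS and Physical examination sections as follows.

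1. **Examiner-assessed outcomes.** Have TCSS, foot examination and blood pressure at T1 and T2 done by the blinded physician already named, or by existing staff who deliver no part of the programme and are kept unaware of allocation. Both conditions are needed: a nurse who merely delivers no module to that patient may still know the arm.
2. **Questionnaires.** Have them completed in one mode at T0, T1 and T2, without programme-delivering staff administering them. Baseline is now researcher-administered, so a change made only at T1 and T2 would introduce a mode difference into the repeated-measures comparison.
3. **The claim.** Restrict the assessor-blinded label to the examiner-assessed outcomes.
4. **Limitations.** State in the Discussion that PHDI is reported by unblinded patients and is open to social-desirability bias as well as recall bias.

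The article describes the study as not yet recruiting, so these are changes to staff roles and wording. They add no patients, visits or measurements. The cost is some scheduling effort and a more modest blinding claim. Patient-level reporting bias in PHDI would remain.
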